The inclusion criteria for subjects with asthma are based on international recommendations, including lung function parameters (25), a gestational age over 37 weeks with an inconspicuous peripartal/postnatal period, and presenting an acute asthmatic attack at study enrollment. The definition of subjects with a wheeze is based on previously published data (26–29), including a history of at least two obstructive bronchitis episodes and acute wheezing at study enrollment, as well as an inconspicuous peripartal/postnatal period. Patients (chronic bronchitis and asthmatics) suffering from acute wheezing, respiratory illness, dyspnea, chest tightness, etc. (acute respiratory symptoms) were classified as “exacerbators.” The recruitment of wheezers is clinically and scientifically promising because underlying mechanisms of whether wheezers will develop chronic asthma are not sufficiently understood. Epigenetic signatures/environmental factors are likely to play important roles in disease development and persistence of symptoms (30, 31). We aim to analyze similarities between wheezers and asthmatics to make the diagnosis at the early stages of the disease and to discover potential biomarkers for the clinical routine. Moreover, subjects with no chronic diseases or chronic medication and an inconspicuous neonatal period were classified as healthy controls (age range: 3 months to 65 years of age). The healthy pediatric controls will be age- and sex-matched with diseased children (preschool asthmatics/wheezers and asthmatics). The recruitment of healthy adults will be helpful for correlation analyses of age-dependencies. In the future, we are also planning to include adult asthmatics. This is currently in consideration with the entire study members.

All individuals will be observed on the basis of two follow-up (FU) visits to recognize how the “active” and “non-active” phases are presented and differ, respectively (Figure 2).

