**Figure 2 F2:**
[figure not shown]
Flowchart of the pediatric exacerbation study network. Study design is characterized by baseline, first and second FU visits. At each study visit, different biomaterials and clinical item parameters will be obtained.

In detail, at baseline and second FU visits, serum and plasma samples will be collected in monovettes purchased from Sarstedt®. Serum samples will be kept in the dark for 20 min before centrifugation. Plasma samples will be centrifuged upon collection (2.000×g for 15 min). Two-hundred microliter supernatant (serum/plasma) will be transferred to cryotubes, and the samples will be stored at −80°C until experimental use. Furthermore, the blood collection during both visits comprises also PBMC collection. Lithium-heparin/ethylenediaminetetraacetic acid blood tubes (Sarstedt, ORT) will be filled up with blood. The blood volume will be diluted with phosphate-buffered saline (Biochrom, ORT) and overloaded on Biocoll (Biochrom, ORT) in an appropriate ratio, as described in the literature. Afterward, centrifugation at 300 × g for 30 min will be taken place. Carefully, the PBMCs will be aspirated and transferred to a new column tube, and after several phosphate-buffered saline washing steps and cell calculating, the PBMCs will be diluted in fetal bovine serum, dimethyl sulfoxid (and DMEM) in an appropriate ratio as described in the literature and stored until experimental use. In addition, the nasal and pharyngeal swabs will be directly stored at −80°C until microbiome and fungiome analyses. The microbiome project is still under publication elsewhere. The methods will be shortly presented here. After DNA isolation of the swabs, a previously established protocol for 16S- and 18S-rRNA will be used. Region-specific primers will be chosen, and the region-of-interest will be transcribed and amplified through PCR steps. Finally, a barcode will be adapted to the amplified template and via NGS, the microbiome and fungiome libraries will be bioinformatically analyzed and correlated to the clinical item parameters. The microbiome project is still under publication elsewhere, and the fungiome project is currently in the establishing stage. The fungal sequencing steps will be adapted as published by Illumina® (https://emea.illumina.com/content/dam/illumina-marketing/documents/products/appnotes/its-metagenomics-app-note-1270-2018-001-web.pdf).

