**Questionnaire (summarized item parameters)**
i. Age and sex at study enrollment
ii. Place of birth, mode of birth, gestational weeks, birth height and weight
iii. Postnatal complications, including infections, mechanical ventilation
iv. Duration of breastfeeding
v. Vaccination
vi. Pet owner
vii. Allergic symptoms including itch, rhinitis, conjunctivitis, and duration of allergic symptoms
viii. Atopic eczema
ix. Family history for atopic disorders
x. Recurrent respiratory symptoms at preschool period
xi. Chronic medication and the response to this medication
xii. Asthma control test score
xiii. Current symptoms (e.g., cough, chest tightness, wheezing, and fever)

The study recruitment started in January 2018 and will be finished on 31/12/2021. All patients with typical symptoms requiring study enrollment will be presented at the emergency room of the (affiliated) university children's hospitals, and a study enrollment protocol will be obtained. Participating study centers are Center of Child and Adolescent Medicine, Helios University Hospital Wuppertal of Witten/Herdecke University, Germany and Children's Hospital, and Helios Hospital Niederberg, teaching hospital of University Hospital Essen/Germany. All participated subjects and/or their parents/legal guardians provided written informed consent. Healthy controls will be recruited mostly from children of teammates of the study centers, or the following alternatives may be considered for the recruitment of healthy children and adolescents, e.g., calls in social platforms, flyers for day-care centers, schools, private practices, social institutions, newspapers, and internet. These announcements will be separately reported to the ethics committees in advance.

A patient stratification in subgroups (atopic vs. non-atopic, transient vs. seasonal-dependent vs. multi-triggered vs. single-triggered vs. permanent wheezers, steroid-independent or steroid-dependent phenotypes) were based on clinical (questionnaire) and laboratory parameters (e.g., immunoglobulin E) (32).

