All analyzed biomaterials and data involving human participants are in accordance with ethical standards and with the Helsinki declaration (1964) and its later amendments or comparable ethical standards. Ethical approval and later amendment approvals are obtained by the Ethics Committees of Witten/Herdecke University and Ärztekammer Nordrhein, and the study is registered at the German Clinical Trials Register (DRKS). All experiments, including the data extraction and analyses, were and will be obtained pseudonymously. The obtained subject-relevant information and biomaterials were and will be separately coded with study-relevant numbers and codes. All subject-relevant data and experimental results will be filled in a database to perform correlation analyses. With this coding strategy, except the (deputy) study head, nobody may follow retrospectively to patient-sensitive information. All biomaterials were processed according to established internal standard operating procedures and were stored at −80°C or in liquid nitrogen until experimental use. The study recruitment is still ongoing, and the current subject and biomaterial numbers allow first pilot experiments and statistical analyses. The description of the collected data will be done on the basis of statistical parameters. Insofar as the distribution of the data enables, the comparison of the two groups will be carried out using analyses of variance and typical significance tests. Data will be presented as box plots with medians, interquartile ranges, minimum–maximum values or standard deviation, or standard error of the mean. In addition, the data will be presented and analyzed by heat maps, cluster analyses, point clouds, bar, and column charts. Moreover, sequencing results will be normalized within each group, and normalization methods, e.g., DeSeq2, will be performed as previously described by Anders and Huber (33). In addition, metagenomic and proteomic data will be analyzed by professional biostatisticians within our study network. The raw data will be uploaded on separate repository databases, as stated by the journal's requirements. For the experiments, age- and sex-matched stratification will be done between diseased and healthy groups in which each diseased patient will be compared with the same healthy children based on age and sex.

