## Advantages and Pitfalls

This study is a prospective, multicenter, and observational cohort study conducted in two centers in Germany. A disadvantage of our study is the short observation period of our subjects, which is currently limited to 3 months. The study cohort can only be examined at two different time points after the baseline visit. The effects of exacerbation at the longitudinal level cannot be determined yet. Therefore, we are currently planning to establish a longitudinal study with the wheezers to be able to observe the mechanisms behind their development of bronchial asthma in the FU. One consideration here, for example, would be the recruitment of children when being infected with viral infections (e.g., influenza virus, respiratory syncytial virus, or coronavirus). Biomaterials could be collected at different points in time, for example, during exacerbation and FU. In addition, a further pitfall is the reduced motivation of parents and patients to attend FU visits, as is the case in many studies. This presents a major problem to achieve a significant subject number.

A further limitation is a regional dependency during the interpretation of the results. Our study cohort will be recruited in two urban centers, and a comparison cohort living in rural areas is currently not included. Here, supra-regional study centers should be included in the near future. Subsequently, there are also country-specific difficulties in the interpretation of the observed data. Another limitation is the lack of recruitment of adult asthmatics. Although we can compare the data with healthy children and adolescents, we do not have any reliable information on age dependency. We are currently planning an adult cohort and hope to submit the ethics proposal in the foreseeable future.

To handle the sampling procedure homogenously, we established standard operating procedure protocols where each sample should be processed, standardized upon biomaterial collection to reduce the pitfalls between persons. All study relevant materials, e.g., monovettes, swab materials, etc., were tested for suitability before recruiting. The nucleic acid concentration and the cell counts were appropriated during pilot sample processing.

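### Sampling season is not controlled: cases are sampled at an attack and again within 3 months, and controls are matched on age and sex only, so season may be confounded with exacerbation status

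*Protocol article*

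**What the plan says.** Under Methods and Analysis, asthmatics enter during an acute attack and wheezers during acute wheezing, through the emergency room. The date of a case's first sample is thus set by the attack. The same section states: "All individuals will be observed on the basis of two follow-up (FU) visits", with the purpose of contrasting active and non-active phases. For blood, "at baseline and second FU visits, serum and plasma samples will be collected".

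Advantages and Pitfalls names as a disadvantage "the short observation period of our subjects, which is currently limited to 3 months", and adds: "The study cohort can only be examined at two different time points after the baseline visit".

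Healthy controls come mostly from the children of staff, otherwise from public calls and flyers. No link between their sampling dates and those of the cases is stated. Matching is described twice in Methods and Analysis, both times on age and sex only. In the statistics paragraph, "age- and sex-matched stratification will be done between diseased and healthy groups", so that "each diseased patient will be compared with the same healthy children based on age and sex". The group comparisons are analyses of variance and standard significance tests, with no covariate named.

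Season appears only as a clinical label, in the list of wheeze phenotypes: "transient vs. seasonal-dependent vs. multi-triggered vs. single-triggered vs. permanent wheezers". The limitations cover follow-up length, attendance, region and the absence of adult asthmatics, but not sampling season.

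**The concern.** The study looks for environmentally driven changes in the airway: microbiome and fungiome from swabs, cytokines, and non-coding RNA. Such readouts could plausibly change over the year in healthy children too. Two contrasts are then exposed.

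- **Attack versus recovery.** A sample taken up to 3 months after the attack falls at a different point of the year. Within one child, season moves together with visit, so pairing does not remove it.
- **Diseased versus healthy.** Cases are sampled when attacks occur, and controls whenever they are recruited. Age and sex matching does nothing to align the calendar.

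If attacks cluster in part of the year and a marker has a yearly cycle, part of an apparent exacerbation signature would be ordinary seasonal change. That matters in a study meant to deliver diagnostic biomarkers of exacerbation.

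**Working it through.** **The article's own figures.** The article contains no sample size or power calculation to reproduce. Its recruitment count does reproduce: 62 wheezers + 55 asthmatics + 59 healthy = 176.

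**Inputs from the article.** Second follow-up within 3 months, taken here as exactly 3 months, or 90 degrees of the year; n = 55 asthmatics; 59 controls, including adults.

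**Assumptions (not in the documents).**
- The marker follows a yearly cosine of amplitude A = 0.25 SD.
- Case enrolment density is proportional to 1 + k·cos(t), where k = (r − 1)/(r + 1) for a peak-to-trough ratio r.
- Attack peak and marker peak coincide.
- The within-child correlation is 0.5, so the SD of the paired difference is 1.
- Testing is two-sided at 5%.

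**Formulas.**
- Mean seasonal shift after m months: (A·k/2)·(1 − cos(2πm/12)). At m = 3 this is A·k/2.
- Paired test: z = shift·√55. False-positive rate: Φ(z − 1.96) + Φ(−z − 1.96).
- Diseased versus healthy, controls sampled evenly over the year: the shift is again A·k/2, with standard error √(1/55 + 1/59) = 0.187. This uses all 59 controls, which is generous because they include adults.

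| Enrolment peak:trough | k | Shift (SD) | z, paired | False positives, paired | False positives, 55 vs 59 |
|---|---|---|---|---|---|
| 1:1 (even) | 0 | 0 | 0 | 5.0% | 5.0% |
| 2:1 | 0.33 | 0.042 | 0.31 | 6.1% | 5.6% |
| 4:1 | 0.60 | 0.075 | 0.56 | 8.6% | 6.9% |
| trough of zero | 1 | 0.125 | 0.93 | 15.3% | 10.2% |

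With the 62 wheezers in place of the 55 asthmatics, the paired rates are 6.2%, 9.1% and 16.6%.

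**Sensitivity.**
- *Amplitude and sample size.* With all 117 diseased children paired and A from 0.2 to 0.5 SD, the paired rate is 6.5% to 14.7% at 2:1 and 9.9% to 36.8% at 4:1.
- *Clustering beyond the cosine model.* The mean shift can be written A·R, where R is the concentration of attacks; cosine enrolment caps R at 0.5. With R = 0.8, nearly all attacks fall in one short season, and A = 0.25 gives a shift of 0.20 SD and a rate of 32%.
- *Phase.* If the marker peaks an angle φ after the attacks, the 3-month shift is (A·k/2)·(cos φ − sin φ). It is zero when the marker peaks 1.5 months after the attacks, √2 times larger when it peaks 1.5 months before, and reversed in sign at other phases.
- *Visit length.* The factor (1 − cos(2πm/12)) is 1 at 3 months, 2 at 6 months and 0 at 12 months.

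**The case against.** The strongest reply is that no bias has been shown. The article gives no monthly distribution of attacks, no seasonal variation of any marker and no dates for control sampling. One phenotype label among five wheezer strata does not establish that enrolment bunches. All of this stands. A reader might infer that seasonal change will be reported as an exacerbation effect, or that large false-positive rates are to be expected. The documents do not support either inference: with even enrolment the mean shift is zero, and with moderate clustering the inflation is small.

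A reader might also blame the 3-month follow-up itself. That does not hold either. In the model a 6-month visit doubles the shift, and only a same-season visit removes it. The article already lists the short follow-up as a disadvantage.

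Further replies stand in part:

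- **Recruitment from January 2018 to the end of 2021 covers every season.** Coverage is not balance, because clustering that repeats each year survives pooling over years.
- **Covariates and contrasts may be set out in a fuller plan that is not shown.** This is true of the model terms. The matching factors, however, are stated in the article, and they leave season out.
- **Swabs and nasal brushings may not be taken at both visits.** The text fixes timing at baseline and second follow-up for blood; the visit flowchart is not visible. The attack-versus-recovery point is therefore firm for blood and conditional for the other materials.
- **Viruses and pollen are candidate triggers, not only nuisance.** This is fair. Subtracting the controls' change answers a narrower question, so both estimates should be shown.

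**Conclusion.** The concern holds as a risk of confounding. Case sampling is tied to the attack, recovery sampling falls within 3 months, and matching is on age and sex only. Nothing stated keeps season apart from exacerbation status in either contrast, and the limitations do not mention it.

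The size cannot be determined from the documents. With A = 0.25 SD, aligned peaks, correlation 0.5 and 55 pairs, the false-positive rate is 5% under even enrolment, about 6% to 9% at 2:1 to 4:1, and 15% or more only under extreme clustering. Larger amplitudes or more pairs raise these figures; other phases can raise, cancel or reverse the shift. The remedy needs no new visits and improves on the stated comparison, so the change should be made.

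**What to change.** 1. Keep age and sex matching. Add calendar time of sampling as a covariate in the diseased versus healthy comparisons, either as a yearly sine and cosine pair or as season.
2. Where feasible, time the remaining control recruitment to follow case enrolment.
3. For markers sampled at both visits, report the baseline-to-second-follow-up change in diseased children, and next to it that change relative to the change in healthy children over the same interval. The article has all individuals return, so these visits are already planned.
4. Name sampling season among the limitations.

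**Cost.** The covariate uses two parameters as a sine and cosine pair and somewhat widens intervals. Subtracting the controls' change costs more. With SD 1 for each change, the standard error goes from 1/√55 = 0.135 to √(1/55 + 1/59) = 0.187. That is about 1.4 times as wide even if all 59 controls return and are usable, which is a further reason to show both estimates. Strict month matching should not be required: there are only 59 controls, adults included, for 117 diseased children, and a narrow calendar window on top of age and sex would leave few matches.

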## Methods and Analysis

To counteract to this concern, we have built a clinically prospective, multicentered, observational exacerbation cohort to provide deeper insights. Starting in winter 2018, we have now established a pediatric exacerbation network in Germany. The study recruitment is currently ongoing, up to date having already recruited 176 study subjects having chronic bronchitis/wheezing episodes (age group <6 years, *n* = 62), children and adolescents with bronchial asthma (age group >6 years, *n* = 55) presenting recurrent asthma attacks, as well as healthy children, adolescents, and adults (*n* = 59). Currently, our biomaterial collection comprises approximately 2,500 specimens, including sera, plasma, cells, swabs, and sputum.

The study cohort comprises two diseased groups (acute exacerbated wheezers and asthmatics) and healthy children and adults. The subjects will not undergo any interventional/allergic provocations.

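### At current counts, distinct 1:1 age and sex matching covers at most half of the diseased children, and the named tests do not use age or sex; adjust for both and keep every child

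*Protocol article*

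**What the plan says.** All references are to the Protocol article, Methods and Analysis.

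- **Counts.** The opening paragraph says recruitment is still open, "up to date having already recruited 176 study subjects". The groups are "chronic bronchitis/wheezing episodes (age group <6 years, *n* = 62"), "children and adolescents with bronchial asthma (age group >6 years, *n* = 55") and "healthy children, adolescents, and adults (*n* = 59").
- **Controls.** The eligibility paragraph describes the healthy controls as "age range: 3 months to 65 years of age". It states that "The healthy pediatric controls will be age- and sex-matched with diseased children", and gives healthy adults a separate use, the study of age-dependencies.
- **Matching rule.** The statistics paragraph calls the procedure a stratification by age and sex between diseased and healthy groups, for the experiments. It then adds that "each diseased patient will be compared with the same healthy children based on age and sex". No ratio is stated.
- **Tests.** The same paragraph names analyses of variance and typical significance tests for comparing groups, where the distribution allows, and DESeq2-type normalisation for sequencing data. Neither age nor sex is mentioned as a term in any model.

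**The concern.** The matching rule refers to each diseased patient, yet there are about twice as many diseased children as healthy subjects, and some of the healthy subjects are adults. If the rule is taken as one distinct control per patient, the controls run out at half of the patients or sooner.

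Two things are at stake. Exacerbating children are hard to recruit, so an analysis confined to patients with their own control would lose precision. And if the control pool matches the patients only partly, an unadjusted group test leaves differences in age and sex between the groups. Those could be mistaken for disease effects in markers that vary with age, which is a real possibility in a cohort running from infancy through adolescence.

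**Working it through.** **Inputs (opening paragraph of Methods and Analysis).** Wheezers under 6 years: 62. Asthmatics over 6 years: 55. Healthy subjects: 59, adults included.

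**Stated total.** 62 + 55 + 59 = 176, which agrees with the article.

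**Patients to be matched.** 62 + 55 = 117.

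**Ceiling for distinct 1:1 pairs.** Maximum pairs = min(117, 59 − adults). The number of adults is not given, so it is varied as an assumption.

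| Adults among the 59 (assumed) | Paediatric controls | Share of patients with own control | Patients without | Patients per control if all are covered |
|---|---|---|---|---|
| 0 | 59 | 59/117 = 50.4% | 58 | 1.98 |
| 10 | 49 | 49/117 = 41.9% | 68 | 2.39 |
| 20 | 39 | 39/117 = 33.3% | 78 | 3.00 |
| 30 | 29 | 29/117 = 24.8% | 88 | 4.03 |

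These shares are upper bounds, because age and sex must also line up. The two patient groups lie on opposite sides of age 6, so a closely age-matched control can hardly serve both.

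**Recruitment needed to close the gap.** Distinct pairs for all 117 need 117 − 59 = 58 more paediatric controls if no present control is an adult, and 68, 78 or 88 more in the other rows. This assumes that no further patients enrol.

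**What keeping every child is worth.** As an illustration, take the difference in means detectable with 80% power at two-sided 5%, in SD units: (1.960 + 0.842) × √(1/n1 + 1/n0).

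| Paediatric controls (n0) | All 117 patients against n0 | n0 patients against n0 controls |
|---|---|---|
| 59 | 0.447 | 0.516 |
| 49 | 0.477 | 0.566 |
| 39 | 0.518 | 0.634 |
| 29 | 0.581 | 0.736 |

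The calculation pools the two patient groups. It ignores both any gain from matching and any precision lost to age imbalance when adjusting. It shows direction and rough size only.

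**The case against.** The strongest reply is that the article never commits to 1:1 matching without reuse. Its sentence begins with stratification between groups, sets no ratio, and can mean children of the same age and sex, or controls that are openly shared. Either is feasible with 117 patients and 59 healthy subjects. Recruitment is open until 31/12/2021, with several further routes to healthy children listed, so the counts are a snapshot. The rule applies to the experiments, which may use subsets. Ratio, age tolerance and reuse are details that an article may leave to a fuller document.

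All of this stands, and it rules out several stronger readings that a reader might infer:

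- *That the matching is impossible.* This is true only of distinct 1:1 pairs for every patient at current counts.
- *That patients will be dropped or controls reused without disclosure.* The article says neither.
- *That adults confound the disease contrasts.* They are counted in one healthy group, "as well as healthy children, adolescents, and adults", but the article matches paediatric controls only, compares patients with healthy children, and gives adults another purpose.
- *That type I error is inflated.* If 59 controls were evenly reused to form 117 pairs and those pairs analysed as independent, the variance would be understated by (1/117 + 1/59)/(2/117) = 1.49, and a nominal 5% test would reject about 10.9% of the time before any gain from matching. The article does not describe that analysis. A group comparison that counts each child once has no such inflation, and ignoring positive correlation within genuine pairs usually makes a test conservative.

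The reply does not remove the gap between the matching and the tests. Current numbers are said to be enough for first pilot experiments and statistical analyses, so the imbalance bears on work already under way. However the matching is read, the named tests leave age and sex out.

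**Conclusion.** The point holds in a limited form. At current counts distinct 1:1 pairs can cover at most 59 of 117 diseased children (50%), and between 25% and 42% if 10 to 30 of the healthy subjects are adults. Comparing every patient on age and sex therefore depends on shared controls, strata or further paediatric recruitment, and the named tests do not carry the matching variables into the analysis.

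The 50% ceiling rests only on the article's counts. The lower shares rest on assumed numbers of adults, and all would change as recruitment proceeds. The size of any residual age or sex confounding cannot be computed, because the age and sex distributions by group are not given. This is a worthwhile, low-cost improvement to the analysis, not evidence that the planned comparisons are invalid.

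**What to change.** 1. Analyse the disease contrasts by regression, entering all diseased children and all healthy children once each, with sex and a flexible age term (for example a spline) as covariates. Include the same terms in the sequencing count models.
2. State explicitly that healthy adults enter only the age-dependency analyses, as the eligibility paragraph implies.
3. Direct the remaining control recruitment at age-sex strata where healthy children are few relative to patients.
4. Where an experiment uses a matched subset, either match without reuse or use matched-set or cluster-robust inference, and report how many patients were left out.
5. Reword the matching sentence so that it says whether matching is individual or by stratum, and whether controls are shared.

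**Cost.** Age and sex are already on the questionnaire, so no new data or participant procedures are needed. The changes are to analysis wording and to which healthy children are sought next. The price is a small reliance on the age model, greatest where one group has few children of a given age.
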